## 4 Investigational plan

### 4.1 Overall study design and plan

This is a randomized, open-label, parallel group, 2-arm multicenter study to investigate the efficacy and safety of anakinra in reducing hyper-inflammation and respiratory distress in adult patients with severe COVID-19 and CSS pneumonia.

The study consists of screening, a 2-week treatment period and a 2-week follow-up period.

The 2-week treatment period is open, and the patients will be randomized to treatment with anakinra + standard of care or standard of care alone in a 1:1 ratio.

Anakinra will be administered as 4-times daily i.v. infusions for a maximum of 15 days (Days 1 to 15), according to the patient health status and expert clinical opinion. The primary endpoint will be evaluated at Day 15.

According to hospital internal protocol, if the patient improves enough to recommend his/her discharge before the 15th day of the study, the patient will be able to continue receiving the medication at home by s.c. administration (100mg/6 hours). In any case, follow-up visits by telephone or in person will be made, depending on where the patient is, until the end of the study.

The study duration for an individual patient will not exceed 4 weeks. The end of the study is defined as last patient last follow-up visit/phone call.

Figure 1:

[figure not shown]

The study design has a total sample size of 180 patients and consists of two stages. At the end of the treatment stage, the success rates are compared between each arm: anakinra + standard of care treatment vs standard of care alone.

A data review committee composed of experts in internal medicine will be involved in the study oversight and interpretation of the study results.

## 4.2 Discussion of study design, including the choice of control groups

## 4.3 Selection of study population

### 4.3.1 Inclusion criteria

A patient must fulfill the following criteria in order to be included in the study:

- Age 18-80 years.
- Severe pneumonia COVID-19 defined as:
  - Nasopharyngeal smear with RCP positive for SARS-CoV-2
  - X-Rays (or other technique) pulmonary infiltrates compatible with pneumonia.
  - 1 or more of the following criteria:
    - Ambient air oxygen saturation  $\leq 94\%$  measured with a pulse oximeter.
    - Pa:FiO2 (partial pressure O2/fraction of inspired O2)  $\leq 300$ .
    - Sa:FiO2 (O2 saturation measured with pulse oximeter/ fraction of inspired O2)  $\leq 350$ .
- High suspicion of CSS that could resemble MAS-like: represented by IL-6 values  $> 40$  pg/mL and/or ferritin  $> 500$  ug/L and/or PCR  $> 30$  mg/L (rationale:  $\geq 5$  upper normal limit) and/or LDH  $> 300$  UI/L. We have chosen these parameters because they are implemented in all the participating hospitals, they are a reflection of the cytokine storm and they have also been significant in terms of predicting mortality in patients with COVID-19 (9).
- Written informed consent. The protocol will be explained to the patient in front of a nurse who will act as a legal witness by signing the document on behalf of the patient.

#### 4.3.2 Exclusion criteria

The presence of any of the following will exclude a patient from inclusion in the study:

- Need for oro-tracheal intubation and/or invasive mechanical ventilation at the start of the study.
- AST/ALT with values greater than 5 times normal levels.
- Neutrophils < 1.500 cell/mmc.
- Platelets < 50.000 cell/mmc.
- Sepsis or pneumonia documented by other pathogens than SARS-CoV-2.
- Existence of any life-threatening comorbidity or any other medical condition that, in the investigator's opinion, makes the patient unsuitable for inclusion.
- Inability to obtain informed consent.
- Positivity for HBV or HCV.
- Patient with active tuberculosis (It is at the discretion of the researcher to perform the tuberculin test on the patient in the screening period if it is considered a risk population and on patients with active tuberculosis manifestations).
- Pregnancy.
- Use of other previous or concomitant biological treatments. Patients in concomitant treatment with other biologicals that may interfere will be excluded: tocilizumab, canakinumab, TNFalfa inhibitors, JAKinibs
- Severe renal dysfunction (estimated glomerular filtration rate  $\leq 30$  ml / min / 1.73 m^2) or receive continuous renal replacement therapy, hemodialysis or peritoneal dialysis.
- Uncontrolled hypertension (sitting systolic blood pressure > 180 mmHg or diastolic blood pressure > 110 mmHg).
- Administration of plasma from convalescent patients who have recovered from SARS-CoV-2 infection.
- History of hypersensitivity or allergy to any component of the study drug.
- Enrollment in another concurrent intervention clinical trial, or intake of an investigational medication within three months or 5 half-lives prior to inclusion in this study, if deemed to interfere with the objectives of this study as assessed by the investigator.

- Predictable inability to cooperate with given instructions or study procedures.

#### 4.3.3 Withdrawal of patients from treatment or study

##### 4.3.3.1 *Withdrawal from treatment*

A patient should be withdrawn from the study treatment if, in the opinion of the Investigator, it is medically necessary, or if it is the wish of the patient.

When a patient is withdrawn, the date of last IMP (investigational medicinal products) administration and the date and reason for treatment withdrawal should be clearly described in the relevant sections of the CRF. If a patient is removed from treatment because of an AE, the reason for treatment withdrawal should always be stated as 'adverse event' irrespective of whether this was the investigator's or the patient's decision.

If a patient withdraws due to worsening of disease, patient should be treated as a non-responder. In these case, the patient will be able to receive treatments that are protocolized at their hospital. The patient could be treated with pulses of steroids, intravenous immunoglobulins, betainterferon and other biologic or immunosuppressants agents such as cyclosporin, tacrolimus, baricitinib, tocilizumab, sarilumab, ruxolitinib...

The patient will continue to participate in the study without taking study treatment.

##### 4.3.3.2 *Withdrawal from study*

Whenever possible and irrespective of the reason for withdrawal, the patient should be examined as soon as possible. Relevant samples should be obtained, and all relevant assessments should be completed. The CRF should be completed as far as possible. Date and reason for the study withdrawal should be clearly described in the CRF.

#### 4.3.4 Replacement of withdrawn patients

Patients withdrawn from the study will not be replaced.

#### 4.3.5 Screening failures

Screening failures are defined as patients who consent to participate in the study but are not subsequently randomized into the study. A minimal set of screening failure information is required which includes demographics, reason for screen failure and failed eligibility criteria.

Patients who do not meet the criteria for participation in this study (screening failure) may not be rescreened.

## 4.4 Treatments

### 4.4.1 Treatments administered

According to the randomization schedule, patients in arm A will receive (IMP) and standard of care and patients in arm B will receive standard of care only, see Table 1.

The treatment standard of care will be based on hydroxychloroquine and/or lopinavir-ritonavir and/or azithromycin.

Table 1:

| Arm | Investigational product | Dosage form | Route         | Daily dose                                                                                           | Dosage regimen              |
|-----|-------------------------|-------------|---------------|------------------------------------------------------------------------------------------------------|-----------------------------|
| A   | Anakinra                | Solution    | i.v. infusion | Days 1-15: 400 mg/day in total, divided into 4 doses given every 6 hours                             | 4 times daily for 15 days   |
| A   | Hydroxychloroquine      | Tablets     | Oral          | Day 1-15: 400 mg/day in total, divided into 2 doses given every 12 hours (loading dose: 400 mg/12 h) | 2 times daily for 5 days    |
| A   | Lopinavir-Ritonavir     | Tablets     | Oral          | Day 1-15: 800/200 mg/day in total, divided into 2 doses given every 12 h                             | 2 times daily for 5-7 days. |
| A   | Azithromycin            | Tablets     | Oral          | Day 1-15: 500 mg /day                                                                                | 1 time daily for 5 days.    |
| B   | Hydroxychloroquine      | Tablets     | Oral          | Day 1-15: 400 mg/day in total, divided into 2 doses given every 12 hours (loading dose: 400 mg/12 h) | 2 times daily for 5 days    |
| B   | Lopinavir-Ritonavir     | Tablets     | Oral          | Day 1-15: 800/200 mg/day in total, divided into 2 doses given every 12 hours                         | 2 times daily for 5-7 days. |
| B   | Azithromycin            | Tablets     | Oral          | Day 1-15: 500 mg /day                                                                                | 1 time daily for 5 days.    |

---

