#### *4.5.4.8 Electrocardiograms*

A 12-lead ECG recording will be performed at screening and at Day 15 and recorded in the CRF. The ECG assessments will be performed at site and will be reported as “normal” or “abnormal”. Any abnormalities should be specified. Abnormalities reported at screening should be recorded as medical history.

For AE reporting of abnormalities, see Section 4.5.4.3.

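### Table 1 gives each background drug two different durations in both arms, and the hydroxychloroquine daily total conflicts with a loading dose whose period is not stated

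*Protocol*

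**What the plan says.** Table 1 in section 4.4.1 lists three background drugs under each arm, six rows in all. The day range and daily amount stand in the Daily dose column; frequency and duration stand in the Dosage regimen column.

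- **Hydroxychloroquine:** "Day 1-15: 400 mg/day in total, divided into 2 doses given every 12 hours (loading dose: 400 mg/12 h" beside "2 times daily for 5 days".
- **Lopinavir-ritonavir:** "Day 1-15: 800/200 mg/day in total, divided into 2 doses given every 12 h" beside "2 times daily for 5-7 days".
- **Azithromycin:** "Day 1-15: 500 mg /day" beside "1 time daily for 5 days".

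The entries for arms A and B are the same in substance. In the anakinra row the day range is also Days 1 to 15, but there the regimen column says "4 times daily for 15 days", so the two columns match.

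The visit descriptions in 4.5.1.3 to 4.5.1.5 send the reader back to 4.4.1 for study drug administration. Section 4.4.5 covers the timing of anakinra only, and the background therapy paragraph (4.4.7.1) covers methylprednisolone only. On cardiac monitoring, section 4.5.4.8 states: "A 12-lead ECG recording will be performed at screening and at Day 15 and recorded in the CRF".

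**The concern.** If the day range means dosing days, as it does for anakinra, all six background rows prescribe two different courses. A site that follows one column departs from the other, while section 7.4 prohibits waivers and requires deviations to be documented. Hydroxychloroquine has a second difficulty: a fixed daily total is stated from Day 1 alongside a loading dose that exceeds it.

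These drugs form the base to which anakinra is added in arm A and the listed treatment in arm B. Sites that read the table differently would give materially different amounts of the same drugs. That adds variation in background exposure that the design did not intend, and it leaves the prescriber without a clear instruction on drugs given to patients in both arms. The reading chosen also determines whether the later scheduled ECG falls during or after background treatment.

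**Working it through.** The protocol states no cumulative dose, so there is no figure to reproduce. The check is daily dose × days under each column, with all inputs from Table 1.

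**Duration conflict, no loading dose**

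| Drug | Daily dose column (15 days) | Dosage regimen column | Ratio |
|---|---|---|---|
| Hydroxychloroquine | 400 × 15 = 6,000 mg | 400 × 5 = 2,000 mg | 3.0 |
| Azithromycin | 500 × 15 = 7,500 mg | 500 × 5 = 2,500 mg | 3.0 |
| Lopinavir/ritonavir, 5 days | 800/200 × 15 = 12,000/3,000 mg | 800/200 × 5 = 4,000/1,000 mg | 3.0 |
| Lopinavir/ritonavir, 7 days | 12,000/3,000 mg | 800/200 × 7 = 5,600/1,400 mg | 2.14 |

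**Hydroxychloroquine loading dose**

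A dose of 400 mg every 12 hours is 2 × 400 = 800 mg in a day, twice the stated total of 400 mg/day. The number of loading days is not given, so call it L (an assumption). For a course of D days:

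total = 800 × L + 400 × (D − L)

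| L (assumed) | D = 15 | D = 5 | Ratio |
|---|---|---|---|
| 0 | 6,000 mg | 2,000 mg | 3.0 |
| 1 | 6,400 mg | 2,400 mg | 2.67 |
| 2 | 6,800 mg | 2,800 mg | 2.43 |
| 5 | 8,000 mg | 4,000 mg | 2.0 |

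Setting the longest reading with one loading day against the shortest without any gives 6,400 / 2,000 = 3.2. The threefold figure therefore describes the duration conflict alone.

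**ECG timing, assuming the background course starts on Day 1**

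The Day 15 visit has a window of ±2 days, so it falls between Day 13 and Day 17. A 5- or 7-day course ends on Day 5 or Day 7, and no scheduled ECG after screening falls within it. A 15-day course ends on Day 15, so that ECG falls within it unless it is done on Day 16 or 17.

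**The case against.** The best defence is that Days 1 to 15 is only the name of the treatment period. Section 4.5.1.5 uses it that way, and sections 4.1 and 4.4.5.1 treat 15 days as a maximum for anakinra. On this view the first column gives the period and daily amount, the second gives the duration, and a site can satisfy both. The reading is possible, but the table does not state it. The anakinra row pairs the same range with a 15-day duration, and a daily amount attached to a day range is ordinarily read as dosing on those days. The ambiguity stands.

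Four other objections limit how far the point goes.

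- A reader might infer that the loading dose is itself a second, incompatible regimen, or that it affects all three drugs. It concerns hydroxychloroquine only, and a loading dose is by nature higher than maintenance. The defect is the unstated loading period and a daily total that cannot hold on a loading day.
- A reader might infer bias between arms, since treatment is open-label. The entries are the same in both arms, and the permuted blocks in 4.4.3 are intended to balance arms within centers. Differential use by arm is possible in any open-label trial, but nothing in Table 1 produces it.
- A reader might infer that correcting the table would give every patient one common background. It would not. Section 4.4.1 allows any combination of the three drugs, section 1.3 ties care to the usual protocols, and sections 4.4.7.1 and 4.4.7.2 leave further treatment to the investigator. But freedom over which drug to use does not explain two printed durations for the same drug.
- The ECG point depends on when background treatment starts, which the protocol does not fix; it may already be running at screening. It is a consistency check that follows from the correction, not a separate defect.

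**Conclusion.** The point holds as an internal contradiction in the operative dosing table. All six background rows carry a day range that disagrees with the stated duration, and no other section resolves it. Taken literally, cumulative exposure differs 3.0-fold for azithromycin and for hydroxychloroquine without loading, and 2.14- to 3.0-fold for lopinavir-ritonavir. Those ratios need only the table's own figures. The hydroxychloroquine figures with loading (2.67-fold for one day under both durations) rest on an assumed loading period.

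The consequence is avoidable between-site variation in background exposure and a patient-safety ambiguity in both arms. The documents do not support a claim of systematic difference between arms, and no effect on the primary comparison, its power or its type I error has been shown.

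**What to change.** Reconcile the day range with the duration column for each background drug in Table 1, with the same text in both arms. Reconcile the hydroxychloroquine daily total with its loading dose and state when the loading dose applies. A range such as the 5-7 days for lopinavir-ritonavir need not become a single number; what is needed is that the two columns agree. Then check that the ECG schedule in 4.5.4.8 and Table 3 is consistent with the reconciled courses. Which regimen is right is for the sponsor's clinicians to state.

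The cost is a correction to one table and a notice to sites. The table correction itself needs no extra patients or procedures.

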#### 4.4.2 Identity of investigational medicinal products

Possible deficiencies related to the handling and quality of the IMP should be reported in the CRF and also directly to [[contact]](mailto:[contact]).

##### 4.4.2.1 *Anakinra*

The IMP anakinra is delivered as a sterile solution for injection, prefilled in a single-use syringe with the strength 100 mg. The total volume of injection is 0.67 mL and the concentration of anakinra in the solution is 150 mg/mL.

Anakinra must be stored at refrigerated conditions at 2-8 °C (36°-46°F) in a secure area at the study sites. Further instructions for handling and storage of the IMP anakinra are available in the IMP manual.

SOBI, will provide the study drug as well as the packing and distribution. Labeling will comply with national regulatory requirements.

#### 4.4.3 Method of assigning patients to treatment groups

The different treatment groups are;

- Arm A: Anakinra as add-on to standard of care
- Arm B: Standard of care only

The ratio between the treatment groups is 1:1, i.e., the same number of patients will be randomized to anakinra or standard of care.

In order to assign each patient to each of the treatment branches and ensure a balance between them for the different centers, the method of random allocation by permuted blocks of sizes 10 and 12 will be used, using the randomizer library of the R statistical package, version 3.4.0.

Although the study is open, measures are taken to prevent a selection bias: one collaborator from each center will be in charge of the allocation, for which he will receive the identifying information of each recruited subject (trial identification number), attaching the branch indicated by the random procedure and returning this information to the people in charge of continuing the development of the intervention.

#### 4.4.4 Selection of doses

##### 4.4.4.1 Dose selection rationale for anakinra

Anakinra is approved for the chronic treatment of a number of inflammatory diseases as a subcutaneous treatment (at doses of 100 mg/day or in weight-based doses of up to 8 mg/kg/day). The i.v. administration of anakinra has been studied in clinical trials in healthy volunteers and in critically ill patients with sepsis and hyper-inflammation at variable i.v. doses up to 3500 mg/day over 72 hours: e.g., 2 mg/kg/hour, 20 mg/kg/day (<40 kg) and 916 mg/day (> 40kg), bolus of 100 mg followed by infusion of 2 mg/kg/hour. No safety concerns emerged in these studies [(14-18)].

A study in children with systemic onset juvenile arthritis complicated by refractory macrophage activation syndrome is currently ongoing (NCT02780583) in which anakinra is administered at dose of 10 mg/kg/day to a maximum of dose of 200 mg/day divided every 12 hours (for children  $\leq$ 40 kg) or 5 mg/kg/day up to a maximum dose of 400 mg/day divided every 6 hours (children > 40 kg and adults).

Based on the above, in this study anakinra is administered at a total dose of 400 mg per day, divided in 4 i.v. doses of 100 mg every 6 hours.

##### 4.4.4.2 Rationale for the use of glucocorticoids

Interim WHO guidance argues against the use of glucocorticoids in the treatment of patients with SARS-CoV-2 infection. “They should be avoided, because of the potential for prolonging viral replication as observed in MERS-CoV patients, unless indicated for other reasons” (<https://www.cdc.gov/coronavirus/2019-ncov/hcp/clinical-guidance-management-patients.html>). However, evidence demonstrating a positive effect or a detrimental effect of glucocorticoids specifically in the treatment of patients with SARS-CoV-2 infection is lacking. In real life, glucocorticoids are being widely used in the treatment of patients in China (6).

For SARS-CoV-2 infection, a growing body of evidence shows that hyper-inflammation appears to be particularly prominent in patients with severe disease, as well as in non-survivors compared to survivors (20, 21). All together these results point to high ferritin, high D-dimers and high LDH levels as being associated with poor outcome. Furthermore, initial data show the presence of hyperproduction of inflammatory cytokines with a profile similar to that present in patients with secondary hemophagocytic lymphohistiocytosis (sHLH) (20).

As glucocorticoids are one of the mainstays of first line anti-inflammatory treatment in sHLH, they have been suggested as one of the potential treatments for patients with severe SARS-CoV- 2 infection (22). Further to the relevance of the hyper-production of inflammatory cytokines in this infection, initial promising data have been reported with the use of IL-6 targeted therapies, namely tocilizumab, in the treatment of patients with SARS-CoV-2 infection (23). Noteworthy, in this report all patients treated with tocilizumab also received glucocorticoids.

As this study is testing the hypothesis of the efficacy and safety of cytokine-targeted anti-inflammatory treatments in patients with SARS-CoV-2 infection and hyper-inflammation, it appears useful to evaluate these anti-inflammatory treatments with a background of glucocorticoids. Indeed, in sHLH, anakinra is used with a background treatment of glucocorticoids (24, 25, and 26).

A recent paper has reported the efficacy of a therapeutic approach consisting of intravenous continuous anakinra infusions in treating severely ill adult patients with sHLH/MAS. Continuous infusion of i.v. anakinra may result in rapid serologic and subsequent clinical improvement in adult patients with MAS. This method for treating cytokine storm should be considered in the current COVID-19 pandemic in the subgroup of patients with severe disease that have a cytokine storm presentation (27).

Based on anakinra benefit published by Adam Monteagudo et al. (27), a course of 1 pulse of i.v. methylprednisolone for 3 consecutive days (pulse dose recommendend 250-500 mg) should be considered under investigators clinical criteria in both arms at anytime during the study .

#### 4.4.5 Selection and timing of doses for each patient

##### 4.4.5.1 *Anakinra*

Anakinra will be administered by i.v. infusion at total dose of 400 mg per day, divided in 4 doses 100 mg i.v. every 6 hours.

Anakinra treatment will continue for a maximum of 15 days (Days 1 to 15) if needed, according to clinical response and HCP prescription. The date and time of each anakinra administration will be recorded in the CRF.

Before administration, the full content of the prefilled, single-use syringe (anakinra 100 mg) will be diluted in 10 mL saline. The i.v. administration of anakinra must occur immediately after the preparation over an infusion period of 5 minutes.

Full instructions for the preparation of anakinra are available in the IMP manual.

#### 4.4.6 Blinding and unblinding

This is an open study with no level of blinding.

#### 4.4.7 Concomitant therapy

##### 4.4.7.1 *Background therapy*

A course of 1 pulse of IV methylprednisolone for 3 consecutive days (pulse dose recommended 250-500 mg) should be considered under investigators clinical criteria in both arms at any time during the study.

